### Statistical Methods

#### General Principles

Selection of patients for exposure to treatment based on clinical features and physician preference instead of random allocation inevitably introduces opportunities for bias and confounding. According to the principles of Good Research for Comparative Effectiveness Research (GRACE) [4] and in line with the HTA recommendations for non-randomized studies [19], appropriate control of confounding variables and pre-specification of analytical techniques is implemented as one of the primary requirements for high-quality comparative effectiveness research. In addition, rigorous risk-based centralized monitoring is introduced to enhance the validity of the observational trial further.

#### Effectiveness Evaluation

Ordinal analysis of the modified Rankin scale (mRS) three months after stroke onset is chosen as a clinically relevant primary endpoint for final treatment effects. The leading secondary endpoint is the NIHSS score on days 21 and 90.

The technical operationalizations for the first-line analysis of the primary and secondary effectiveness measures, based on observed cases (OC) and target population (see section Analysis Sets), are as follows:

•Primary outcome measures (effectiveness evaluation)•Secondary outcome measures (effectiveness evaluation)

1.Ordinal modified Rankin Scale (mRS) at 3 months after stroke onset, absolute scores, Mann-Whitney Effect Size (MW) [20–25], OC, Target Population;2.Ordinal NIH Stroke Scale (NIHSS) at 21 days and 3 months after stroke onset, absolute scores, Mann-Whitney Effect Size (MW), OC, Target Population;3.Ordinal modified Rankin Scale (mRS) at 21 days after stroke onset, absolute scores, Mann-Whitney Effect Size (MW), OC, Target Population;4.Proportion of patients with excellent recovery (mRS score 0–1) at three months after stroke onset, Odds Ratio, OC, Target Population;5.Proportion of patients with functional independence (mRS score 0–2) at three months after stroke onset, Odds Ratio, OC, Target Population;6.Ordinal MoCA at 3 months after stroke, Mann-Whitney Effect Size (MW), OC, Target Population.

According to the ICH Guideline E9 (ICH Topic E9, Statistical Principles for Clinical Trials, Step 4, Consensus guideline, 5 February 1998, CPMP/ICH/363/96) the results will be given as P-values as well as effect size measures with their associated confidence intervals (outcome no. 1, 2, 3, 6: Mann-Whitney effect size; outcome no. 4 and 5: odds ratio, supplemented by Mann-Whitney effect size for inter-outcome comparisons [25]), so that the direction and quantity of the treatment effects are determined with their precision.

The Mann-Whitney effect size [20–25] is the most valuable effect size measure for nonparametric approaches based on the well-known Wilcoxon framework because it is valid in data situations where the Hodges-Lehmann shift parameter is no longer appropriate. Furthermore, the Mann-Whitney effect size is appropriate for continuous, ordinal, and binary data at the same time and represents an ideal effect size measure. Incidentally, the 25^th^ Anniversary of the journal Statistics in Medicine dedicated a whole issue to papers about the Mann-Whitney statistic [20].

The Mann-Whitney effect size measure (MW) gives the probability that a randomly chosen subject of the test group is better off than a randomly chosen subject of the comparison group, defined in statistical shortcut: P (X<Y) + 0.5 P (X=Y). The null and alternative hypothesis for the comparison of Cerebrolysin vs. placebo can be formulated as follows (superiority test) by applying the Mann-Whitney effect size measure:

[figure not shown]

The traditional benchmarks for the Mann-Whitney effect size measure (MW) are as follows [26, 27]:

[figure not shown]

The global alpha of the trial is 0.05 two-sided. The primary outcome measure will be analyzed according to the pre-defined Bauer-Koehne alpha for stage I of the trial (see section 0). However, the secondary outcomes will be analyzed using the same alpha, applying the principle of a *priori* ordered hypotheses (fixed sequence) for multiplicity control. If the test for superiority concerning the primary outcome measure shows statistical significance, the secondary criteria can be tested with the same alpha as the first test with complete control of the study-wise type I error. The sequence and nature of the a *priori* ordered test-statistical hypotheses are defined above (outcome measures no. 1–6). The procedure of a *priori* ordered hypotheses is most potent with full control of alpha (for control of alpha using stepwise testing see [28]).

#### Safety Evaluation

The operationalizations for the evaluation of the pre-defined safety measures, based on observed cases (OC) and intention-to-include (ITI) population, are as follows:

1.Mortality, Odds Ratio, OC, Target Population;2.Serious Adverse Events, Odds Ratio, OC, Target Population;3.Adverse Events, Odds Ratio, OC, Target Population.

These safety measures will be used for group comparisons. In addition to the Target Population analysis with control of confounders, sensitivity analyses will be performed based on the ITI population. Adverse drug reactions to Cerebrolysin (ADR), serious adverse drug reactions to Cerebrolysin (SADR), and suspected unexpected serious adverse reactions to Cerebrolysin (SUSAR) will be displayed for the Cerebrolysin treatment group.

#### Case-Mix Standardization

The patient groups are standardized using nonparametric multilevel stratification procedures combined with a “restricted cohort” design to minimize enrollment bias. The individual risk factors have been identified from previous research results on NIHSS predictor variables, allowing appropriate control for confounders of outcome after acute ischemic stroke. The pre-specified case-mix standardization strategy follows the recommendations of the GRACE Principles for Good Research on Comparative Effectiveness [4, 5].

Pre-Defined Clinical Predictor Variables [29]:

1.Initial NIHSS;2.Small Vessel Disease (yes-no);3.Prior Stroke (yes-no);4.Prior Diabetes (yes-no);5.Prior disability (yes-no);6.Age.

The operational definitions of variables no. 2 to 6 for consistent application across all participating sites are provided in the operational manual of the trial. The combination of the above variables is a highly efficient predictor for outcome after ischemic stroke [29], making an additional control of infarct volume dispensable due to comparable areas under the receiver operator characteristic (ROC) curves [29].

The top-level case-mix standardization is based on the initial NIHSS score as one of the strongest predictors for outcome after stroke [29–31]. The top-level control is performed by implementing stratification per NIHSS score unit with subsequent meta-analytic pooling of strata (i.e., comparing groups within identical baseline NIHSS score) (Figure 1). The eligibility restriction to NIHSS 8-15 allows full stratification for each possible baseline score (leading to a total of eight top-level strata).

**Figure 1. F1:**
[figure not shown]
Case-Mix Standardization.

The pre-planned method for synthesis of the strata based on the primary Mann-Whitney (MW) effect size measure [20–25] is the Wei-Lachin test of stochastic ordering (one-dimensional test) [32], a maximin-efficient robust test (MERT) [33, 34] which provides a combined MW estimate and test of overall treatment effect from the pre-defined ensemble of independent strata.

The second level case-mix standardization is performed to control further confounders (see pre-defined clinical predictor variables). It is implemented within each of the top-level NIHSS strata by means of nested sub-strata and subsequent adjustment through the Cochran-Mantel-Haenszel (CMH) pooling procedure (also known as the van-Elteren procedure) [35]. The nested sub-strata are based on the following pre-defined clinical predictor variables (see above):

•Diabetes (yes-no);•Small Vessel Disease (yes-no);•Age (<65 – ≥65 years).

The combination of the three binary predictor variables results in a total of eight nested sub-strata. Technically the robust Peto-Wilcoxon test with CMH pooling of sub-strata was chosen, providing adjusted MW across sub-strata with associated confidence intervals. This procedure allows unbiased adjustment of ordinal or binary data also in the presence of very low sample sizes (only sub-strata with total N<3 are excluded from CMH analysis).

In addition to the specified multilevel case-mix standardization, controlling four out of the six pre-defined predictor variables, a specific method to strengthen observational, non-interventional studies is introduced for control of the two remaining confounders (“prior stroke” and “prior disability”): the “restricted cohort” design, i.e., patients are only eligible for this trial without prior stroke and prior disability. Restricted cohort design is one of the measures recommended for high-quality comparative effectiveness research [19]. This way, any risk of bias associated with the specific confounders can be avoided.

The described case-mix standardization for control of confounders is performed for all comparative effectiveness evaluations, resulting in an adjusted overall effect size with an associated confidence interval for each defined endpoint. The same applies to the comparative safety evaluations to minimize confounding (see, e.g., FDA Guidance to Industry on Reporting Safety Studies) [36]. Unadjusted safety analyses, including all available patient data, will be performed as additional sensitivity analysis.

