#### Treatment

Cerebrolysin is a neuropeptide preparation with marketing authorization to treat cerebrovascular disorders and neurodegenerative diseases for many years worldwide. Since its first approval, stroke therapy has developed, and new treatment concepts have been implemented. In addition, over time, Cerebrolysin treatment in stroke has evolved with different time windows, dosages, and duration of therapy, often being given pragmatically by physicians. Therefore, the main aim of this study is to capture these variables of Cerebrolysin treatment and its comedication in patients with moderate to severe neurological deficits after acute ischemic stroke to guide further research.

C-REGS 2 is an international, non-interventional, prospective registry study to observe clinical practices of routine use of Cerebrolysin in patients with moderate to severe neurological deficits after acute ischemic stroke in a controlled and open-label manner. According to local treatment standards, all patients receive acute stroke care, which is not amended or influenced by the study. The outcome of Cerebrolysin-treated patients is compared with control group patients, who do not receive Cerebrolysin to evaluate the safety and effectiveness of Cerebrolysin in routine practice.

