### Investigational Product

Cerebrolysin has marketing authorization in the countries participating in C-REGS 2. C-REGS 2 is an observational study. Thus, the treatment of patients follows standard hospital practices and is separated from the decision to include a patient in the study.

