#### Dosage, Formulations, and Administration

Dosage, frequency, duration, and mode of administration of Cerebrolysin follow the local hospital practice following the terms of the local marketing authorization and are not amended or influenced by the study. Prescribed Cerebrolysin will be used as a solution for injection/concentrate for solution for infusion.

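### Site and country are missing from the case-mix strata and from the variance, so if Cerebrolysin use differs between hospitals the MW estimate can be biased and its interval too narrow

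*Protocol article*

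**What the plan says.** The Treatment section states: "C-REGS 2 is an international, non-interventional, prospective registry study". Study Design adds that it is multicentre. On who is treated, Investigational Product says that "the treatment of patients follows standard hospital practices and is separated from the decision to include a patient in the study". On background care, the Treatment section says: "According to local treatment standards, all patients receive acute stroke care, which is not amended or influenced by the study".

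The adjustment is set out in Case-Mix Standardization. The top level is one stratum per NIHSS point from 8 to 15, eight in all, combined by the Wei-Lachin procedure as independent strata. The second level lies within each NIHSS stratum: "The nested sub-strata are based on the following pre-defined clinical predictor variables", namely diabetes, small vessel disease and age below or from 65 years. This gives eight sub-strata, pooled by the van Elteren procedure. The article counts this as "controlling four out of the six pre-defined predictor variables" and handles the other two, prior stroke and prior disability, by excluding such patients. The same scheme is applied to all comparative effectiveness and comparative safety evaluations.

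Sites are mentioned for consistent variable definitions, for raters independent of treatment administration, and for on-site monitoring. Neither site nor country enters the strata, the pooling or the variance.

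**The concern.** If hospitals differ in how readily they use Cerebrolysin, the hospital is a possible common cause of exposure and outcome. Acute care follows local standards and concomitant medication is unrestricted, so care that affects 90-day mRS can also differ by hospital. Within one of the planned cells, a treated patient from one country may then be compared with an untreated patient from another.

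Two separate errors would follow. Confounding by hospital would shift the MW estimate away from its true value. In addition, a variance that treats patients of one hospital as independent would be too small, because exposure and outcome would both cluster by site. The assumption of independent strata does not help, since one hospital's patients fall into several NIHSS strata.

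At stake is the stage I decision, which allows a stop with success at p1 ≤ 0.0299, and every later claim based on the same scheme. The Prospective Meta-Analysis section applies the same operationalizations to the companion registry, so the gap carries over.

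**Working it through.** **Inputs from the article.** Global alpha 0.05 two-sided; futility bound 0.3; stage I success bound 0.0299; stage II product bound 0.0087; stage I after about 30% of enrolment; total 1745 before and about 2000 after the dropout allowance; MW to be detected 0.55.

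**Inputs assumed, because the article does not give them.** Patients per site, number of sites, intra-site correlation (ICC) of mRS, and the spread of Cerebrolysin use between sites.

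**1. The plan's own bounds.** The product bound is exp(−χ²₄,₀.₉₅/2) = 0.0087. The level is 0.0299 + 0.0087 × ln(0.3/0.0299) = 0.0500. Both agree with the article, so the nominal threshold is taken as stated.

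**2. The adjustment set.** 8 NIHSS strata × 8 sub-strata = 64 cells, or 1745/64 ≈ 27 patients per cell. None is defined by site or country.

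**3. Variance only, treatment decided wholly by site.** The design effect is DE = 1 + (m − 1) × ICC for m patients per site. The nominal two-sided 0.0299 corresponds to z = 2.171, and the true error is 2 × [1 − Φ(2.171/√DE)].

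The value of m matters. Stage I has about 0.3 × 1745 ≈ 524 to 0.3 × 2000 = 600 patients. If a site contributes 40 at full enrolment and accrual is proportional, it has 0.3 × 40 = 12 at stage I. Forty per site at stage I would mean only about 13 to 15 sites.

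| ICC | DE, m = 12 | True error | DE, m = 40 | True error |
|---|---|---|---|---|
| 0.01 | 1.11 | 3.9% | 1.39 | 6.6% |
| 0.02 | 1.22 | 4.9% | 1.78 | 10.4% |
| 0.03 | 1.33 | 6.0% | 2.17 | 14.0% |
| 0.05 | 1.55 | 8.1% | 2.95 | 20.6% |

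**4. Bias and variance together, by simulation.** Settings: no true effect, N = 1745 over 50 assumed sites, seven-level mRS, van Elteren weighting over the 64 cells, a single look at nominal 5%, and use varying by site with an SD of 1.5 on the logit scale. This approximates the planned pooling; the Wei-Lachin step was not reproduced.

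| ICC | Correlation of site use with site outcome | 64-cell analysis: mean MW | Type I error | Stratified by site: mean MW | Type I error |
|---|---|---|---|---|---|
| 0.05 | 0.3 | 0.522 | about 35% | 0.500 | 4.4% |
| 0.05 | 0 | 0.499 | about 12% | 0.500 | 5.6% |
| 0.02 | 0.3 | 0.514 | 15% to 19% | 0.501 | 4.8% |

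In the second row the average reported standard error was 0.0146, against an actual spread of 0.0186. In the first row the bias of 0.022 is 0.022/0.05 = 44% of the shift the study is sized to detect. The site-stratified test used site alone, which was sufficient only because simulated treatment did not depend on case mix within a site.

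**5. The condition.** When every simulated site treated the same share, there was no bias and no understated variance (type I error 5% to 6%).

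**6. Nesting site inside the 64 cells.** With 50 sites, about 5% of patients stayed in usable cells and the standard error rose from about 0.015 to 0.073.

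**The case against.** The strongest objection is that the article does not show hospital to be the main driver of treatment. General Principles attributes selection to clinical features and physician preference, which allows treated and untreated patients in the same hospital. Investigational Product says that treatment follows hospital practice, not that hospitals treat all or none. The sentence beginning "Dosage, frequency, duration, and mode of administration of Cerebrolysin follow the local hospital practice" concerns how the drug is given, not who receives it. Cerebrolysin is authorised in all participating countries, so licensing does not separate the groups. All of this stands. A reader might infer that exposure is strongly tied to site and that the intervals are therefore certainly too narrow; the article supports neither statement, and both problems depend on use varying between hospitals.

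A reader might also attach the 6.6% to 21% range to stage I without qualification. That requires 40 patients per site already at stage I. If 40 is the final count, 3.9% to 8.1% applies.

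There are also safeguards: the Rankin Focused Assessment, mandatory scale training, raters independent of treatment administration, and central statistical monitoring. They reduce rating differences and support data quality. They do not adjust the comparison for differences in care or correct the variance.

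Finally, the SAP is not shown and may contain a site sensitivity analysis. That could soften the point but does not remove it, because the article lists the confounders and the pooling method of the primary analysis in full, and site is not among them.

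**Conclusion.** The point holds in conditional form. The stated primary method omits site and country from both the adjustment and the variance, in a registry where the article itself ties treatment to hospital practice. To the extent that use differs between hospitals, the MW estimate can be biased by differences in hospital care, and its interval and p-value will be too optimistic.

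The size cannot be derived from the article. The figures for error at the stage I threshold rest on assumed site sizes and ICC and on treatment decided wholly by site, so they are near the worst case for variance. Confounding bias comes on top and does not shrink with enrolment; its simulated size rests on an assumed correlation between a site's use and its outcome level. The omission should be corrected, but it does not show that the study's result will be wrong.

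**What to change.** - Keep the stratified MW test as the primary analysis, but base its interval and p-value on a site-clustered variance, for example a site-level bootstrap. This addresses the variance, not the bias.
- Pre-specify a key within-site sensitivity analysis of 90-day mRS. One option is a van Elteren test stratified by site (by country where a site has only one group) with coarser case-mix cells. The other is a proportional-odds model with site effects plus NIHSS, age, diabetes and small vessel disease.
- Do not nest site inside the 64 cells, which would leave few usable patients.
- Report the Cerebrolysin share by site and the number of sites with only one group, and interpret the primary result alongside the within-site estimate.

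The cost is analysis-plan wording and analysis time; the only extra variable is the enrolling site. Single-group sites add nothing to the within-site estimate, so its interval is wider. The model option adds a proportional-odds assumption, which the article's Discussion prefers to avoid, so it is better placed as a sensitivity analysis than as the primary test.

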#### Two-Stage Procedure

The two-stage adaptive procedure of Bauer P and Köhne K (1994) is chosen as the sequential method. The two-stage procedure based on Fisher’s combination test (Bauer and Köhne) shows only a negligible loss in test power as compared to a fixed sample size study but allows early stopping due to success or failure [37]. Furthermore, assumptions for sample size calculation can be rechecked after stage I. The same applies to design modifications within the framework of the adaptive approach, although this is not the rationale for introducing the two-stage procedure in this study. The formal Bauer-Köhne *futility* benchmark is set for this study to α_0_=0.3. It is important to note that this benchmark takes into account the limited number of available patients for a possible stage II due to the restricted cohort design.

With a global multiple level alpha=0.05 two-sided, and defined futility level of α_0_=0.3 the following decision structure will be formally established (p_1_=P-value of stage I, p_2_=P-value of stage II):

Decision Structure for Stage I results (two-sided)

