**Table d95e520:** 

p_1_≥α_0_=0.3	: stop because of futility
p_1_ϵ (0.0299; 0.3)	: continue with stage II
p_1_≤α_1_=0.0299	: stop with success (rejection of H_0_)

Decision Structure for Stage II results (two-sided)

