**Table d95e551:** 

p_1_p_2_>α_c_=0.0087	: stop because of futility
p_1_p_2_≤α_c_	: rejection of H_o_ (proof of efficacy)

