### Sample Size

As this is an observational study, the relations among effect size, sample size and power estimates are indicative only. However, some justification is needed to support the planning of the number of centers and the duration of the enrolment period.

Formal nonparametric sample size calculation was performed to allow detection of “small” group differences in the ordinal comparative effectiveness evaluations with 90% power.

The sample size calculations are based on the following design specifications:

a.Two-sided type I error defined as alpha=0.05 (multiple level alpha);b.90% power (1 – beta);c.Effect size measure for ordinal scales: Mann-Whitney measure of superiority (MW) [20–25, 38–40];d.Difference to be detected: MW=0.55 (equivalent to a “small” difference according to Cohen [26, 27]);e.Assumed maximum imbalance between enrolled groups: 1:2;f.Two-Stage Adaptive Design with α_0_=0.3; Stage I sample size=30% of total sample size (r_subsample I_=0.3); power compensation for defined two-stage parameters based on Newton Cotes-algorithm of fifth order [41];g.Nonparametric model: stochastic superiority (minimized assumptions).

In the presence of the above assumptions, the calculated total sample size results in 1745 subjects (including power adjustment for the chosen parameters of the two-stage procedure). For compensation of usual ambiguities (dropouts etc), the calculated sample size is enhanced by a factor of 1.15 (15%) from 1745 to a total of approx. 2000 subjects. This way, at least 90% power is guaranteed within the framework of the two-stage procedure.

Stage I is completed after enrollment of about 30% of the planned total patients (r_subsample I_=0.3).

Nonparametric sample size calculations within the framework of a Two-Stage procedure (Bauer-Köhne) [41] were based on the model of stochastic superiority and have been performed applying the validated software Nnpar 1.0 and Bauer-Köhne 4.0 from IDV Data Analysis and Study Planning, Krailling/Munich).

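### The stage II rule multiplies two-sided p-values without asking the stages to agree in direction, so it can call conflicting stages proof of efficacy and gives up about 2 points of power

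*Protocol article*

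**What the plan says.** The Two-Stage Procedure section of the protocol article names a "two-stage procedure based on Fisher’s combination test (Bauer and Köhne") and sets the frame "With a global multiple level alpha=0.05 two-sided". Both decision tables below it are headed as two-sided.

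- Stage I stops for futility at "p_1_≥α_0_=0.3" and for success at "p_1_≤α_1_=0.0299". Between these bounds the trial continues.
- Stage II compares the product p1·p2 with 0.0087. At or below that value the table reads "rejection of H_o_ (proof of efficacy").

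Neither table gives a sign condition or a stage weight. The Sample Size section fixes "Stage I sample size=30% of total sample size", so 70% is left for stage II. The article allows design changes after stage I, "although this is not the rationale for introducing the two-stage procedure in this study".

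**The concern.** A two-sided p-value measures distance from the null and discards the side. A product of two such values is equally small whether the stages support or contradict each other. There are two consequences.

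- **Interpretation.** The table attaches an efficacy claim to a set of outcomes that includes one stage favouring Cerebrolysin and the other favouring control.
- **Efficiency.** Part of the type I error allowed at stage II goes to conflicting outcomes, which are rare when the treatment works. The bound for agreeing stages must then be stricter than it need be.

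**Working it through.** **Inputs.** From Two-Stage Procedure and its tables: overall alpha 0.05 two-sided, α1 = 0.0299, α0 = 0.3, product bound 0.0087. From Sample Size: 30% of patients in stage I, MW = 0.55, allocation 1:2, N = 1745 (about 2000 after the 1.15 factor). Assumed here: Noether variance, no ties, no stratification loss, futility applied as written.

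**1. The plan's alpha reproduces.** α1 + c·ln(α0/α1) = 0.0299 + 0.0087 × ln(0.3/0.0299) = 0.0299 + 0.0087 × 2.306 = 0.0299 + 0.0201 = 0.04996. The bounds are valid at 0.05.

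**2. Share spent on conflicting stages.** Stage II rejections take 0.0201 under the null. There, the sign of each stage statistic is independent of its two-sided p-value, so half of these rejections have opposite signs: about 0.0100.

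**3. An example.** Take p1 = 0.03 against treatment and p2 = 0.28 in favour.
- p1 exceeds 0.0299, so the trial continues. The product is 0.0084 ≤ 0.0087, so the null is rejected.
- The signed statistics are -2.170 and +1.080. Size-weighted: √0.3 × (-2.170) + √0.7 × 1.080 = -1.189 + 0.904 = -0.28 (p = 0.78).

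**4. Power of the stated rule at MW = 0.55, N = 1745.**
- Total noncentrality: 0.05 × √(12 × 2/9 × 1745) = 3.411. By stage: 3.411 × √0.3 = 1.868 and 3.411 × √0.7 = 2.854.
- Early success 38.1%, futility stop 20.1%, continue 41.8%.
- Integrating over stage I gives 36.3% success at stage II. Power is 38.1% + 36.3% = 74.4%.

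**5. Comparators with the same N, α1, α0, split and overall alpha.** The signed 30/70 rule has critical value 2.027. The directional Fisher rule multiplies one-sided p-values taken in the same direction. Its bound is (0.025 - 0.01495)/2.306 = 0.00436.

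| Rule (MW = 0.55, N = 1745) | Power |
|---|---|
| Stated product of two-sided p-values | 74.36% |
| 30/70 weights added, p-values still two-sided | 74.49% |
| Directional Fisher, equal weights | 76.61% |
| Signed inverse-normal, equal weights | 76.70% |
| Signed inverse-normal, 30/70 weights | 76.82% |

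Direction alone adds 76.61 - 74.36 = 2.25 points. Weights alone add 0.13, or 0.12 once the statistics are signed (76.82 - 76.70).

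**6. Other settings, stated rule against signed 30/70 rule.**

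| MW | N | Stated | Signed 30/70 |
|---|---|---|---|
| 0.55 | 2000 | 79.6% | 81.4% |
| 0.54 | 1745 | 55.4% | 59.7% |
| 0.54 | 2000 | 61.2% | 65.1% |

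At MW = 0.55 and N = 1745, success among trials that reach stage II rises from 87% (36.3/41.8) to 93% (38.7/41.8).

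**The case against.** The strongest defence is that the product test is a published, fully pre-specified procedure whose bounds hold alpha at 0.05, as step 1 confirms. That stands: this is not an error-rate defect. The article also reports effect sizes with confidence intervals so that direction can be read, and the full analysis plan may add a sign condition. That would repair the interpretation. If the bound stayed at 0.0087, however, total alpha would fall to about 0.0299 + 0.0100 = 0.0399 and the power would still be forgone.

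A reader might infer that the loss comes from giving a 30% stage the same weight as a 70% stage. The rule is indeed unweighted and can fail the stronger of two pooled results. With both stages in the same direction, p1 = 0.03 with p2 = 0.28 passes (product 0.0084, size-weighted p = 0.036), while p1 = 0.29 with p2 = 0.031 fails (0.0090, p = 0.017). Equal weighting is not what fails the second pair. An equal-weight directional Fisher rule passes it, since 0.145 × 0.0155 = 0.00225 ≤ 0.00436. The weights are worth only 0.1 to 0.2 points.

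A reader might also infer that a better combination rule would rescue the stated 90% power. It cannot. The futility bound alone stops 20.1% of trials at MW = 0.55 and N = 1745, which caps power at 79.9% under any stage II rule.

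**Conclusion.** The point holds as one of interpretation and modest inefficiency. The stage II rule is blind to direction, and half of its null rejections are conflicts between stages. At the design effect it costs about 2.4 points of power at N = 1745 and 1.8 at N = 2000. At MW = 0.54 the cost is about 4 points. Almost all of this comes from direction and very little from stage size.

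The power figures are asymptotic and rest on the assumptions listed with the inputs. Ties and the stratified test would shift the levels, but should change the comparison between rules little. The documents do not support calling the test invalid. The gap to 90% power is a separate matter.

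**What to change.** Keep N, the two stages, α1 = 0.0299 and α0 = 0.3. Replace the product criterion in the stage II table by: reject if |√0.3·Z1 + √0.7·Z2| ≥ 2.03, where Z1 and Z2 are the signed stage-wise statistics and the weights are fixed now from the planned split. Take the direction of effect from the sign of the combined statistic, and keep the efficacy label for results that favour Cerebrolysin. Rounding 2.027 up to 2.03 is slightly conservative.

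If the sponsor prefers to stay with a product test, a directional Fisher rule does nearly as well: same-direction one-sided p-values with a critical product of about 0.00436.

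The cost is one line in the decision table and the analysis plan and a different combination routine, with no extra patients or alpha. The signed rule departs from the named Bauer-Köhne product test. Its fixed weights are no longer optimal if stage II turns out much smaller than planned, although the test stays valid.
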